[Table 1: Study Schedule for HIV-1 Uninfected Participants (Immediate arm) (Part A) 210](#__RefHeading___Toc75597519)

[Table 2: Study Schedule for HIV-1 Uninfected Participants (Delayed arm) (Part A) 211](#__RefHeading___Toc75597520)

[Table 3: Study Schedule for HIV-1 Infected Participants (Part B) 212](#__RefHeading___Toc75597521)

[Appendix 4 FLIP CHART 213](#__RefHeading___Toc75597522)

[Appendix 5 STUDY INFORMED CONSENT 238](#__RefHeading___Toc75597523)

[Appendix 6 COMPREHENSION ASSESSMENT 250](#__RefHeading___Toc75597524)

[Appendix 7 TOXICITY SCALES 255](#__RefHeading___Toc75597525)

[Table 1: NIAID Toxicity Scale 255](#__RefHeading___Toc75597526)

[Table 2: GILEAD Toxicity Scale 269](#__RefHeading___Toc75597527)

[Appendix 8 TOXICITY ALGORITHMS 274](#__RefHeading___Toc75597528)

[Table 1: Management of Clinical and Laboratory Adverse Events (Except Creatinine) 274](#__RefHeading___Toc75597529)

[Table 2: Management of Creatinine Elevations 275](#__RefHeading___Toc75597530)

[Appendix 9 COUNSELING ASSESSMENT 276](#__RefHeading___Toc75597531)

[Appendix 10 CASE REPORT FORMS (CRF) 277](#__RefHeading___Toc75597532)

PROTOCOL SYNOPSIS

| Study Title: | Phase II Extended Safety Study of Tenofovir Disoproxil Fumarate (TDF) for Prevention of HIV among HIV-1 Negative Men |
| --- | --- |
| Study Sites: | AIDS Research Consortium of Atlanta (ARCA), Atlanta, GA  San Francisco Department of Public Health (SFDPH), San Francisco, CA Fenway Community Health (FCH), Boston, MA |
| Objectives: | Primary Objective:  To determine the clinical and behavioral safety and tolerability of oral daily TDF use as pre-exposure prophylaxis (PrEP) to prevent HIV infection in uninfected men.  Secondary Objectives:  To describe the number of HIV infections and to evaluate whether administration of oral TDF affects the genetic characteristics of HIV-1 breakthrough viruses  To assess social and behavioral effects associated with participation in this safety trial  To evaluate participants’ adherence with daily TDF |
| Design: | Phase II, double blind, placebo-controlled, equal (1:1:1:1) randomization |
| Population: | HIV negative men who have sex with men (MSM) |
| Stratification: | By site |
| Sample Size: | 400 HIV negative MSM |

| Duration of Study: | 24 months for HIV negative MSM, 12 months following HIV diagnosis for MSM who become infected while participating in the study |
| --- | --- |
| Randomization  R  A  N  D  O  M  I  Z  E  Daily TDF  Daily Placebo  No treatment for 9 months, then daily TDF  No treatment for 9 months, then daily Placebo  Site B  Site A  Site C |  |
| Enrollment: | Over 24 months |
| Main eligibility criteria: | Healthy, HIV-1 negative MSM who reported anal intercourse in the last 12 months |
| Study procedures/frequency: | Physical examinations, behavioral risk assessments, and laboratory analyses at screening, baseline, months 1, 3 and then every 3 months through 24 months of study. |
| Test product, dose, and mode of administration: | TDF 300 mg po QD. |
| Criteria for Evaluation | Safety  Clinical and laboratory adverse events  Risk behavior change  Adherence to study drug  HIV antiretroviral resistance |
| Statistical Methods | The primary endpoints are to assess the safety and tolerability of TDF as determined by the proportion of participants with grade 3 or 4 abnormalities (clinical adverse events and laboratory toxicities occurring after treatment initiation), the difference in reported risk behavior between the immediate and delayed treatment arms, and overall rates of adherence. Intent-to-treat analysis will be used. |

GLOSSARY OF ABBREVIATIONS AND DEFINITION OF TERMS

| 3TC | lamivudine, Epivir® |
| --- | --- |
| 3TC/AZT | lamivudine/zidovudine, Combivir® |
| ACASI | audio-computer administered interview |
| AE | adverse event |
| AIDS | acquired immunodefienciency syndrome |
| ALT (SGPT) | alanine aminotransferase |
| AST (SGOT) | aspartate aminotransferase |
| ART | antiretroviral therapy |
| BUN | blood urea nitrogen |
| CAB | community advisory board |
| CBC | complete blood count |
| CBO | community based organization |
| CK | creatine kinase |
| CLIA | clinical laboratory improvement amendments |
| CrCl | calculated creatinine clearance |
| CRF | case report form(s) |
| CRO | contract research organization |
| d4T | stavudine, Zerit® |
| DHHS | Department of Health and Human Services |
| ddI | didanosine, Videx® |
| dL | Deciliter |
| DNA | deoxyribonucleic acid |
| EFV | efavirenz, Sustiva® |
| EIA | enzyme-linked immunosorbent assay |
| FDA | (US) Food and Drug Administration |
| FTC | Emtricitabine |
| g | gram(s) |
| GCP | Good Clinical Practice guidelines |
| HAART | highly active antiretroviral therapy |
| HBV | hepatitis B virus |
| HBsAg | hepatitis B surface antigen |
| HDPE | high‑density polyethylene |
| HIV | human immunodeficiency virus |
| HIV‑1 | human immunodeficiency virus type‑1 |
| ICH | International Conference on Harmonisation |
| IRB | Institutional Review Board |
| ITT | intent-to-treat |
| kg | kilogram(s) |
| LLN | lower limit of normal range |
| MedDRA | Medical Dictionary for Regulatory Activities |
| MEMS | Medication Event Monitoring System |
| mEq | milliequivalent(s) |
| mg | milligram(s) |
| mL | milliliter(s) |
| mm | millimeter(s) |
| MSM | men who have sex with men |
| NAT | nucleic acid testing |
| NIAID | National Institute of Allergy and Infectious Diseases |
| NRTI | nucleoside reverse transcriptase inhibitor |
| NNRTI | non-nucleoside reverse transcriptase inhibitor |
| NtRTI | nucleotide reverse transcriptase inhibitor |
| NVP | nevirapine, Viramune® |
| PBMC | peripheral Blood Mononuclear Cells |
| PCR | polymerase chain reaction |
| PI | protease inhibitor |
| PK | Pharmacokinetic |
| PMPA | 9-[(R)-2(phosphonomethoxy)propyl]adenine monohydrate (tenofovir) |
| PMPA prodrug | 9-[(R)-2-[[bis[[(isopropoxycarbonyl)oxy]methoxy] phosphinyl]-methoxy]propyl]adenine fumarate (1:1) (tenofovir disoproxil fumarate, tenofovir DF, TDF) |
| PEP | post-exposure prophylaxis |
| PrEP | pre-exposure prophylaxis |
| QD | once daily |
| RNA | ribonucleic acid |
| RT | reverse transcriptase |
| SAE | serious adverse event |
| STI | sexually transmitted infection |
| TDF | tenofovir DF, Viread® |
| UA | Urinalysis |
| ULN | upper limit of normal |

# INTRODUCTION

## Background

It has been estimated that 14,000 persons become infected with the human immunodeficiency virus type one (HIV-1) daily, and approximately 40 million individuals are currently infected worldwide (1). As of January 2003, 859,000 AIDS cases had been reported to the Centers for Disease Control and Prevention (CDC) in the United States, and an estimated 143,904 people are now living with HIV infection (2). Of the approximately 35,000 new infections identified annually in the United States, 32% are among men who report sex with men (MSM) and 17% are acquired through heterosexual sex (2). Although, substantial efforts have been devoted toward microbicide and vaccine development, no biomedical product effective at preventing HIV infection has yet been identified. Current efforts among high risk populations have focused on behavioral strategies, encouraging the reduction in the number of sexual partners, monogamy, and consistent and correct condom use for the prevention of sexually transmitted HIV. However, another effective, easy to use method of prevention is urgently needed.

Current animal and human study data suggest that antiretroviral agents used to treat HIV-1 infection may be efficacious when used following HIV exposure (3-10) and animal data suggest that antiretroviral agents may be efficacious pre-exposure as well (7-9). Recently, a non-nucleoside reverse transcriptase inhibitor (NNRTI), nevirapine, was tested in a small phase I/II clinical trial (3) as a potential chemoprophylaxis agent. Although it was generally well-tolerated, there was evidence of hepatotoxicity, and additional clinical reports suggest that nevirapine might be ill suited for pre-exposure prophylaxis (PrEP) because of its unacceptable frequency of side effects and toxicity, especially among HIV uninfected individuals, (11-15) and the ease in which resistance develops (11-14). Another recently approved antiretroviral, Viread® (Tenofovir disoproxil fumarate [TDF]), a nucleotide reverse transcriptase inhibitor (NtRTI), has a lower toxicity profile and may be a more promising PrEP agent.

The purpose of this study is to assess the clinical and behavioral safety of TDF among HIV-1 negative men for its potential further investigation as a chemoprophylactic agent in the prevention of HIV infection as determined by the proportion of participants in each arm who experience adverse events or report different rates of HIV risk behaviors.

## TDF

### General Information

Tenofovir (9‑[(R)‑2‑(phosphonomethoxy)propyl]adenine monohydrate, PMPA) is an adenine nucleoside monophosphate (nucleotide) analog with activity against retroviruses, including HIV‑1 and HIV‑2 (16,17). Tenofovir is metabolized intracellularly to tenofovir diphosphate (PMPApp), which is a competitive inhibitor of HIV‑1 reverse transcriptase (RT) that terminates the growing DNA chain. Due to the presence of a phosphonate group, tenofovir is negatively charged at neutral pH, thus limiting its oral bioavailability. Therefore, tenofovir disoproxil fumarate (TDF, Viread®, (9-[(R)-2-[[bis[[(isopropoxycarbonyl)oxy]‑ methoxy]phosphinyl] methoxy]propyl]adenine fumarate 1:1) a prodrug of tenofovir was developed. TDF is orally bioavailable in animals and humans and is rapidly converted to tenofovir on absorption (18). Further information regarding TDF, its toxicology, efficacy and safety profile will be reviewed in the below text and is available in the Gilead Investigator’s Brochure (Appendix 1) and Viread® Package Insert (Appendix 2).

### Preclinical Pharmacology and Toxicology

TDF is a nucleotide reverse transcriptase inhibitor (NtRTI) and as such is distinct from nucleoside reverse transcriptase inhibitors (NRTIs). Unlike nucleosides, tenofovir undergoes only two rather than three consecutive phosphorylation steps to its active metabolite PMPApp.

The non-clinical toxicology of TDF has been studied in mice, rats, rabbits, dogs, and rhesus macaques. The principal organs of toxicity following TDF administration were the gastrointestinal tract (rats), kidney, and bone. Nephrotoxicity was the dose-limiting toxicity associated with TDF administration in dogs and monkeys. Reductions of serum phosphate were noted in rats, dogs, and monkeys, and chronic high-dose TDF administration to rats and dogs demonstrated some loss of bone mineral density; this loss seemed to be nonprogressive or minimally progressive between weeks 13 and 42. It is suspected that this osteopenia may be related to accelerated bone resorption secondary to reduction of the intestinal phosphate absorption and/or mild renal phosphate leak that develops with chronic treatment. Osteomalacia was documented in rhesus macaques administered chronic daily administered injections 25x the strength of human doses (Appendix 1).

No adverse effects were detected in studies examining the effects on fertility and early embryonic development in rats or rabbits. TDF was not mutagenic in the in vitro *Salmonella*/*Escherichia coli* mammalian microsome reverse assay with the exception of a minimally positive response seen in one of the studies, which was considered to be equivocal (Appendix 1).

### Clinical Trials

The US Food and Drug Administration (FDA) approved Viread® (TDF) in October 2001 for use in combination with other antiretroviral therapeutic (ART) agents for the treatment of HIV‑1 infection. Over 12,000 patients have participated in clinical trials or expanded access studies involving TDF, and TDF has been shown to be generally safe, effective, and well tolerated. (Appendix 2). The TDF clinical trials program includes seven completed phase I trials (studies 701 [intravenous tenofovir], 909, 914, 917, 919, 930, and 932), one phase I/II trial (study 901), one phase II trial (study 902) and three phase III trials (studies 907, 908, 910) (Appendix 1).

Ongoing clinical studies are examining TDF for use in new populations or for new indications. Three studies are being conducted among HIV-infected pediatric populations to examine a suspension formulation for safety and pharmacokinetics. Other studies are assessing safety when co-administered with adefovir dipivoxil for the treatment of lamivudine-resistant hepatitis B virus (HBV) infection among adult patients co-infected with HIV and HBV and as an intravaginal tenofovir topical gel formulation among HIV infected and uninfected women.

In addition, two ongoing phase III trials, 903 and 934, are being conducted among HIV-1 infected adult participants. Study 903 is a randomized, double-blind three-year trial designed to assess the efficacy and safety of TDF vs. stavudine (d4T) with background therapy of lamivudine (3TC) and efavirenz (EFV). Study 934, initiated in August 2003, is an open-label, multicenter clinical trial that will compare TDF, emtricitabine, and EFV with the combination tablet (lamivudine/zidovudine) and EFV.

### Pharmacokinetics

The pharmacokinetics (PK) of TDF has been specifically evaluated in seven trials (studies 901, 907, 909, 914, 919, 930, and 932). These studies demonstrated that the bioavailability of TDF is enhanced by administration with food, TDF is eliminated by both active tubular secretion and glomerular filtration, and the TDF serum half‑life of ~17 hours and intracellular half-life of 10-50 hours supports a once-daily dosing schedule. Following oral administration of 300mg of TDF to HIV-infected patients in the fasted state, maximum serum concentrations are achieved in 1.0 + .4 hours. Since TDF is eliminated by the kidneys, a dose adjustment is necessary for patients with significant renal impairment. The only significant drug interaction reported is with didanosine (Videx® EC, [ddI]) in which ddI systemic exposures increased when administered simultaneously with TDF (Appendix 2).

### Safety

Numerous clinical studies (901, 917, 902, 903, 907, 908, and 910) have demonstrated TDF to have an excellent safety profile (Appendix 1). Assessment of adverse reactions has been primarily based on four studies among HIV-infected persons (902, 903, 907, and 910) in which treatment-experienced and naïve patients received TDF or placebo as part of their ART regimens for at least 24 weeks. Adverse event rates were comparable between the TDF and placebo groups. In the TDF arms, the most common adverse events were mild to moderate gastrointestinal events, i.e., nausea, diarrhea, vomiting and flatulence, occurring in 3-11% of treatment-experienced patients. In studies 907 and 903, rates of creatinine elevation and hypophosphatemia (serum phosphorus <2.2 mg/dl) were similar between the TDF and placebo groups. Among the TDF study patients, 3-4% experienced a serum creatinine increase of at least 0.5 mg/dL from their baseline level; these increases were generally transient and only two persons exceeded 2.1 mg/dL. Hypophosphatemia was detected in 6-16% of TDF study patients (Investigator’s Brochure). In study 902, none of the patients discontinued the study because of TDF-related serum creatinine elevations or hypophosphatemia (19,20).

In the first 48 weeks of the ongoing phase III study (903) comparing TDF to stavudine (d4T) as the third component of ART, grade 3/4 abnormalities were detected in 29% of persons in the TDF group. Elevations in creatinine kinase (8%) and amylase (7%) were the most frequently reported grade 3/4 laboratory abnormalities. Only 3 patients discontinued the study due to laboratory toxicities. Four participants had serious adverse events (anemia, peripheral neuritis, bronchitis, and gynecomastia) that were considered to be possibly related to study drugs. There were no bone fractures attributed to vertebral compression, minimal trauma, or otherwise considered to be related to study drug. The table below lists the grade 2-4 adverse events reported by at least 3% of TDF recipients in study 903 compared to the d4T arm.

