## Follow-up Visits

Participants assigned to the immediate treatment arms will be scheduled for follow-up visits at 1 and 3 months after enrollment and then at months 6, 9, 12, 15, 18, 21, and 24 (Table 1, Appendix 3). Study visits for participants assigned to the immediate treatment arm are to be completed + 7 days based on the enrollment visit date. Participants assigned to the delayed treatment arms will be scheduled for follow-up visits at 1 and 3 months after enrollment and then at months 6, 9, 10, 12, 15, 18, 21, and 24 (Table 2, Appendix 3). Study visits for participants assigned to the delayed treatment arm are to be completed + 7 days based on their enrollment visit until their initial dispensing visit . After the initial dispensing visit (month 9), study visits for participants assigned to the delayed treatment arm will be completed + 7 days based on their month 9 visit date. Regularly scheduled evaluations will be made on all participants whether or not they continue to receive study product.

The following procedures are to be performed at all visits unless otherwise specified:

*Epidemiologic/Behavioral Risk Assessment*

- ACASI (3, 6, 9, 12, 15, 18, 21, and 24 months)

Clinical assessment

- Symptom-directed physical examination
- Administration of Adverse Events/Intercurrent Illness Form
- Concomitant Medication Form

*Laboratory assessment:*

- Hematology profile
- Chemistry profile
- Urinalysis
- Blood sample for storage
- Plasma
- Peripheral Blood Mononuclear Cells (PBMCs) (12 months for immediate treatment arms, 21 months for delayed treatment arms only)
- HIV-1 rapid whole blood EIA (3, 6, 9, 12, 15, 18, 21, and 24 months)
- DEXA scan **(SFDPH only: 12 and 24 months for immediate treatment arms, 9 and 24 months for the delayed treatment arms)**
- STI testing
- RPR (12 and 24 months)
- Urine for GC and CT (6, 12, 18, and 24 months)

Standardized HIV risk reduction counseling as per enrollment visit

During the 24 months of the study, additional HIV testing may be requested at any time by study participants, or may be performed as required by the protocol in the case of an indeterminate result or to help determine the timing of HIV infection more precisely.

After participants complete all scheduled study visits, they will be contacted periodically until final study closeout. The purpose of these interim contacts will be to update contact information and to inform participants of the progress of and timeline for completing the study.

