## Toxicity monitoring

Blood will be obtained at screening, enrollment and then at each subsequent study visit for toxicity monitoring. Routine toxicity monitoring will consist of the following laboratory tests: hematologic profile, chemistry profile, and urinalysis. DEXA scans will be used for a subset of participants. The severity of laboratory toxicity will be assessed and scored according to established laboratory toxicity scales (Gilead Sciences, Inc. toxicity scale for creatinine and DAIDS toxicity scale for all other laboratory toxicity monitoring [Appendix 7]).

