For a grade 4 clinical event or laboratory abnormality confirmed by repeat testing, study product should be discontinued and participant monitored and managed according to local practice. The participant should be followed as clinically indicated until the event resolves to baseline, stabilizes, or is otherwise explained, whichever occurs first.

If a grade 4 toxicity is confirmed and is considered to be unrelated to study product, study product should be withheld until the event resolves to baseline. Study product can then be restarted at the discretion of the site investigator.

If a grade 4 laboratory toxicity is not confirmed by repeat testing, it should be managed per algorithm for the new toxicity grade.

*Creatinine Elevations*

For a grade 1 serum creatinine elevation (>.5 increase from enrollment level) confirmed by repeat testing, study product should be held until creatinine returns to within .3 mg/dL of enrollment level, at which point participant can be re-challenged with full dose of study drug. If a confirmed grade 1 toxicity reoccurs, study product should be permanently discontinued, and participant monitored until level returns to baseline or stabilizes.

For a grade > 2 serum creatinine elevation (serum creatinine > 2.1) confirmed by repeat testing, study product should be permanently discontinued, and participant monitored until level returns to baseline or stabilizes.

Relationship of adverse event to study product

The Investigator must determine the relationship of the AE to the study product. For each AE, an assessment of the relatedness to the test agent should be made using the following scale:

- Unrelated: Onset of the AE had no reasonable temporal relationship to administration of the study product or a causal relationship to administration of the study product is biologically implausible or the event is attributed to an alternative etiology.
- Possibly Related: Onset of the AE has a reasonable temporal relationship to study product administration and a causal relationship is not biologically implausible.
- Probably Related: Onset of the AE has a strong temporal relationship to administration of the study product that cannot be explained by the participant’s clinical state or other factors and a causal relationship is not biologically implausible.

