## Methods of Analysis

Analysis Populations

Intent‑to‑Treat (ITT) Population

This population will include all participants who are randomized into the study and receive at least one dose of study medication. The exclusion of participants who do not receive study drug is justified by the fact that the decision to not initiate study medication is made with no knowledge of the randomized treatment. Participants with major eligibility violations that are identifiable based on pre-randomization characteristics will be excluded. Participants who receive study medication other than that intended will be analyzed according to the group to which they were randomized.

Analysis of the Conduct of the Study

This population will include all screened participants. Specifically, summaries of the following endpoints will be generated: participant screening, eligibility, participant enrollment, participant disposition and reasons for discontinuation, participant medication compliance, participant compliance with study visits, and protocol violations/deviations. Simple descriptive statistics, including percentages, means, and quartiles will be used to summarize the distribution of these endpoints. In addition, the above analyses will be carried out by clinical site to identify any potential site-specific issues. Participants’ disposition will be tabulated as screened but never enrolled, enrolled but never initiated study product, on-study and continuing with study product, discontinued from study product but continuing follow-up for HIV infection or off-study and not continuing follow-up.

*Types of Outcomes and Statistical Analyses*

The outcomes of interest and their respective analyses can be classified by the following factors:

Type of outcome and number of responses per individual:

A) Time until first occurrence of some specified event –

One response per individual – Cox survival regression

B) Yes/no outcome;

One response – Logistic regression

Multiple responses – Longitudinal binary regression

C) Continuous outcome

In general, counts (e.g. number of partners) will be treated as Poisson distributed

outcomes while laboratory values or transformations of those values (e.g. creatinine level,

log (creatinine level) will be treated as normally distributed outcomes.

One response – Poisson, linear regression

Multiple responses – Longitudinal Poisson, linear regression

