## Safety Analyses for Clinical and Laboratory Measurements

The rate of severe reactions will be used as the primary measure of clinical safety of this study drug. Assessment of product safety will include clinical observation and monitoring of hematologic and chemical parameters. All participants will be monitored for local and systemic adverse reactions during the course of the trial. Participants will be closely monitored for the first 8 weeks after product dispensation and followed for at least 15 months on product.

Adverse experiences will be coded into MedDRA (Medical Dictionary for Regulatory Activities) preferred terms. The number and percentage of participants experiencing each specific adverse experience will be tabulated by severity and relationship to treatment. Overall summaries by treatment will include the number and percentage of participants experiencing: (1) an adverse experience; (2) any moderate, severe, or life-threatening experience; (3) any severe or life-threatening experience; (4) adverse experience judged possibly related, probably related, or definitely related to treatment. Additional summaries will summarize the effect of adverse events on study drug dosing. A separate tabulation of SAEs will also be generated and will provide details including severity, relationship to treatment, onset, duration, and outcome. Adverse events that lead to product or study discontinuation will be listed separately.

Participants who become HIV-1 infected while on study will be monitored in a second part of the protocol (Part B). Both potential benefits and potential detrimental effects of the study product based on secondary endpoint analyses described above will be investigated. Clinical endpoints (major and minor) associated with the disease progression (e.g., setpoint, resistance,) will be recorded. Because few clinical endpoints are expected to be observed to support a quantitative analysis, qualitative case-descriptions will be done.

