Three types of safety analyses will be performed depending on the outcome of interest as described in the next three sections. All safety analyses described will be adjusted for study site and the delayed /immediate treatment group variable. It will be explored whether these factors modify (i.e., effect modifiers) any of the observed outcome – treatment relationships and whether study drop-outs are comparable to either a) all others still on study (missing completely at random) or b) to others still on study within their site by study group (missing at random).

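### The continuous laboratory models name site and timing group as covariates but not the man's own pre-product value, which gives up precision at no saving

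*Protocol*

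**What the plan says.** Protocol section 10.4 sorts outcomes by type. Among continuous outcomes it treats "laboratory values or transformations of those values (e.g. creatinine level" or its logarithm) as normally distributed, in linear regression for one response or longitudinal linear regression for several. The models are fitted in PROC GENMOD and allow for correlation within individuals.

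Section 10.5 supplies the covariates: "All safety analyses described will be adjusted for study site and the delayed /immediate treatment group variable". Neither section names a pre-product value as a covariate or change from baseline as the outcome.

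The values are collected. Section 8.3 says: "Blood will be obtained at screening, enrollment and then at each subsequent study visit for toxicity monitoring". Section 6.3 lists a chemistry profile at enrollment. Section 6.8 lists one at every follow-up visit, including month 9, when the delayed arms first receive product (section 5.3.1).

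Other parts of the protocol do refer to the man's own starting value. Section 9.6 defines the lowest creatinine grade that way: "For a grade 1 serum creatinine elevation (>.5 increase from enrollment level) confirmed by repeat testing". The Safety subsection of the TDF background reports that among TDF patients "3-4% experienced a serum creatinine increase of at least 0.5 mg/dL from their baseline level". On the primary measure, section 10.5 says: "The rate of severe reactions will be used as the primary measure of clinical safety of this study drug".

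**The concern.** The rationale section singles out kidney and bone as the two organ systems that may show long-term toxicity. Threshold events in the kidney are likely to be few. The background table for study 903 shows grade 1 creatinine elevations in 3% of the TDF arm and 2% of the stavudine arm over 96 weeks. A comparison of continuous creatinine and phosphorus is therefore a natural supporting analysis.

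If a man's creatinine is fairly stable over time, a comparison of levels between TDF and placebo carries the lasting differences between men as noise. His own pre-product value removes much of that noise. The protocol states a covariate set for its safety models, and this value, probably the strongest predictor available, is not in it. What is at stake is the width of the confidence intervals for the continuous laboratory differences.

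**Working it through.** **The plan's own figures.** The protocol gives no power, SD or correlation for laboratory values, so there is no laboratory figure to reproduce. Its SAE power table (section 10.3) does reproduce. A two-sided Fisher exact test with 200 per group, 1% under placebo and alpha 0.05 gives 16.9%, 36.0%, 56.3%, 73.5% and 85.5%, against the stated 17%, 36%, 56%, 73% and 85%. It also shows how weak event comparisons are at low rates: 3% versus 1% has 17% power, whatever the type of event.

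**Inputs from the protocol**
- Allocation 1:1:1:1, so 200 TDF and 200 placebo when pooled. Loss is put at 10-20%; taking 15% leaves 200 × 0.85 = 170 per group.
- On-product visits in the delayed arms: after months 1 and 3 their schedule is "months 6, 9, 10, 12, 15, 18, 21, and 24 (Table 2, Appendix 3"). Those after dispensing at month 9 are months 10, 12, 15, 18, 21 and 24, so m = 6. The immediate arms also have six in their first 15 months on product (months 1, 3, 6, 9, 12, 15), and nine in all.
- One pre-product value per man, p = 1.

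**Assumptions not in the protocol**
- Exchangeable within-man correlation ρ of 0.5 to 0.8, with 0.3 as a low case. The only correlation stated, 0.5 in section 10.7, is for adherence.
- SD between men of 0.15 mg/dL for creatinine. This affects only the detectable differences, not the percentages.

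**Formulas**, in units of the outcome variance:
- Variance of a man's on-product mean: V0 = (1 + (m − 1)ρ)/m
- After adjusting for one pre-product value: V1 = V0 − ρ²
- Share removed: ρ²/V0
- Equivalent increase in sample size: V0/V1
- Difference detectable with 80% power: 2.80 × 0.15 × √(V × 2/170)

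For ρ = 0.5: V0 = (1 + 5 × 0.5)/6 = 0.583, V1 = 0.583 − 0.25 = 0.333, share removed = 0.25/0.583 = 42.9%.

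| ρ | V0 | V1 | Share removed | V0/V1 | Detectable, unadjusted (mg/dL) | Detectable, adjusted (mg/dL) |
|---|---|---|---|---|---|---|
| 0.3 | 0.417 | 0.327 | 21.6% | 1.28 | 0.029 | 0.026 |
| 0.5 | 0.583 | 0.333 | 42.9% | 1.75 | 0.035 | 0.026 |
| 0.6 | 0.667 | 0.307 | 54.0% | 2.17 | 0.037 | 0.025 |
| 0.8 | 0.833 | 0.193 | 76.8% | 4.31 | 0.042 | 0.020 |

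**Sensitivity.** With m = 9 the share removed is 45.0% at ρ = 0.5 and 77.8% at ρ = 0.8. With two pre-product values and m = 6 it is 57.1% and 85.3%.

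**The case against.** The strongest objection is that the covariate list is not closed. Section 10.5 does not say that site and timing group are the only adjusters, and a SAP, which is not at hand, could add a baseline term. Nor does section 10.4 say that pre-product visits are left out of the longitudinal responses; if they are in, with treatment varying over time, some baseline information is already used. This stands against any claim that the protocol forbids baseline adjustment. It does not remove the point. Covariates are stated, the pre-product value is not among them, and naming it in advance is better than leaving it to a later choice.

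Second, the size rests on an SD and correlations from outside the protocol. Eligibility limits on creatinine clearance and phosphorus could narrow the spread between men and so lower the correlation. This stands, and it is why the low case of 0.3 belongs beside the main range.

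Third, even unadjusted, the detectable difference of 0.035-0.042 mg/dL is under a tenth of the 0.5 mg/dL rise that marks grade 1 (0.042/0.5 = 8.4%). This also stands: the protocol names no small mean shift as clinically relevant, so the gain is in precision rather than in rescuing a failed analysis.

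Fourth, the background does not establish a renal excess. The same subsection says that "rates of creatinine elevation and hypophosphatemia (serum phosphorus <2.2 mg/dl) were similar between the TDF and placebo groups". The 3-4% figure shows how renal change is measured, not that TDF causes it.

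**Conclusion.** The point holds as an improvement to supporting analyses. The stated models for continuous laboratory values leave out a predictor that is already collected. Under ρ of 0.5 to 0.8, six on-product values and one pre-product value, adjusting for it would remove about 43-77% of the variance of the TDF-versus-placebo difference. At ρ = 0.3 the figure is about 22%. These percentages assume exchangeable correlation and that site and timing group explain little of the spread between men.

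A reader might infer three stronger things, none of which the protocol supports:
- That the estimate is biased. Assignment is randomized in blocks within site, so a chance difference at baseline is already reflected in the standard error; only precision is lost.
- That the trial ignores change from baseline in renal safety. Grade 1 creatinine is defined against enrollment.
- That the primary clinical safety result is weakened. It is an event rate and does not use these models.

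The percentages are shares of the total variance that adjustment could remove. Without adjustment, all of that removable part remains.

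**What to change.** In section 10.5, after the sentence on site and timing group, add: longitudinal models of continuous laboratory values (creatinine, phosphorus and the other chemistry and hematology values) will also be adjusted for the participant's last value before first study product, on the same scale as the outcome. This is the enrollment value in the immediate arms and the month-9 value drawn before dispensing in the delayed arms. The grading of creatinine against enrollment stays as it is.

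This is a free improvement: one sentence, one more model term, and no new visits or samples. The only downside is that a man without a pre-product value needs a simple rule fixed in advance, such as mean imputation or a missing-value indicator. Taking the last available pre-product value should make such cases rare, because screening and enrollment samples exist as well.
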